### **IEC Approval Number:**

## CLINICAL TRIAL SUMMARY

|                                        |                                                                                                                                                                                                                                                                                                                                                                                                                                                                                                                                                                                                                                                           |
|----------------------------------------|-----------------------------------------------------------------------------------------------------------------------------------------------------------------------------------------------------------------------------------------------------------------------------------------------------------------------------------------------------------------------------------------------------------------------------------------------------------------------------------------------------------------------------------------------------------------------------------------------------------------------------------------------------------|
| TITLE (GENERAL)                 | Prospective Randomized Clinical Study to Evaluate the Effect of DiabetEaze Powder in Nutritional Management of Pre-Diabetes & Type 2 Diabetes Mellitus.                                                                                                                                                                                                                                                                                                                                                                                                                                                                                                   |
| TITLE (SCIENTIFIC)              | Open, Realistic, Prospective, Randomized, Controlled, Interventional Clinical Study of DiabetEaze Powder in Nutritional Management of Pre-Diabetes & Type 2 Diabetes Mellitus.                                                                                                                                                                                                                                                                                                                                                                                                                                                                            |
| INVESTIGATOR/
TRIALLOCATION | Pankajakasthuri Ayurveda Medical College & PG Centre, Killy, Kattakada, Kerala and Neyyar Medicity, Kattakada, Trivandrum                                                                                                                                                                                                                                                                                                                                                                                                                                                                                                                                 |
| STUDY OBJECTIVES                | 
Primary objectives:
 
 
❖ Clinical Nutritional Assessment of DiabetEaze Powder in Type 2 Diabetes Mellitus.
 
❖ To assess the variation in Quality of Life in terms of direct symptoms.
 
❖ To assess the role of DiabetEaze Powder in managing nutritional inadequacy in Type 2 Diabetes Mellitus.
 
 
Secondary objectives:
 
 
❖ Assessment of hypoglycaemic effect of DiabetEaze Powder.
 
❖ Assessment of effect of DiabetEaze Powder in Pre-Diabetes.
 
❖ Assessment of reduction in complications.
 
 |
| STUDY DESIGN                    | Open, Realistic, Prospective, Randomized, Controlled, Interventional Clinical Study.                                                                                                                                                                                                                                                                                                                                                                                                                                                                                                                                                                      |
| STUDY POPULATION                | Subjects from OPD of Pankajakasthuri Ayurveda Medical College Hospital, Kattakada, Trivandrum and Neyyar Medicity, Kattakada, Trivandrum, satisfying the inclusion criteria.                                                                                                                                                                                                                                                                                                                                                                                                                                                                              |

|                                        |                                                                                                                                                                                                                                                                                                                                                                                                                                                                                                                                                                                    |
|----------------------------------------|------------------------------------------------------------------------------------------------------------------------------------------------------------------------------------------------------------------------------------------------------------------------------------------------------------------------------------------------------------------------------------------------------------------------------------------------------------------------------------------------------------------------------------------------------------------------------------|
| MAIN INCLUSION CRITERIA         | 
 
1. Willing to sign consent form
 
2. Men and Women aged 40 years or greater and not older than 65 years.
 
3. Subjects with clinical evidence of Type 2 Diabetes Mellitus.
 
4. Subjects of Pre-Diabetes with HbA1c range between 5.7% and 6.4% and/or OGTT range between 140 mg/dl and 199 mg/dl.
 
                                                                                                                                                                                                          |
| MAIN EXCLUSION CRITERIA         | 
 
1. Presence of conditions like Medical, Psychological, Social or Alcohol abuse that would interfere with participation in the trial.
 
2. Subjects with known allergy to any of the ingredients of the drug product.
 
3. Pregnant or Lactating women.
 
4. Subjects with Type1 Diabetes Mellitus.
 
5. Subjects undergoing Insulin therapy.
 
6. Other conditions like CKD, Malignancies etc.
 
7. Post-surgical cases mainly GI diseases.
 
8. Patients under Steroid intake.
 
 |
| EXPECTED NUMBER OF SUBJECTS     | 180                                                                                                                                                                                                                                                                                                                                                                                                                                                                                                                                                                                |
| NAME OF INVESTIGATIONAL PRODUCT | DiabetEaze Powder                                                                                                                                                                                                                                                                                                                                                                                                                                                                                                                                                                  |
| FORMULATION                     | 
Ingredients of DiabetEaze Powder is as follows:
 
Curcuma longa Linn (Haridra)
 
Emblica officinalis Gaertn(Amalaki)
 
Strychnos potatorum Linn (Kataka)
 
Salacia reticulata Linn (Ekanayakam)
 
Carum carvi Linn(Krishna Jeeraka)
 
Mimosa pudica (Lajjalu)
 
Moringa oleifera (Shigru)
 
Tinospora cordifolia (Guduchi)
                                                                                                                                                  |

|                                                           |                                                                                                                                                                                                                                                                                                                                                                                                                                                                                                                                              |
|-----------------------------------------------------------|----------------------------------------------------------------------------------------------------------------------------------------------------------------------------------------------------------------------------------------------------------------------------------------------------------------------------------------------------------------------------------------------------------------------------------------------------------------------------------------------------------------------------------------------|
|                                                           | Andrographis paniculata (Kalamegha)
Artocarpus heterophyllus (Panasa)
Eleusine coracana (Ragi)
Hordeum vulgare (Yava)
Anacardium occidentale (Vrikkaphala)
Theobroma cacao (Rasalaphala)                                                                                                                                                                                                                                                                                            |
| ROUTE OF ADMINISTRATION                            | Oral                                                                                                                                                                                                                                                                                                                                                                                                                                                                                                                                         |
| PROOF OF CONCEPT                                   | This formula of the nutritional supplement is based on traditional knowledge.                                                                                                                                                                                                                                                                                                                                                                                                                                                                |
| INVESTIGATIONAL PRODUCT, MANUFACTURING, AND DOSAGE | 
The study drug DiabetEaze is a poly herbal formulation for providing nutritional support to Pre-Diabetes & Type 2 Diabetes Mellitus. Also, it is aimed to reduce complications and to improve quality of life in Type 2 Diabetes Mellitus.
 
The study drug will be manufactured in GMP certified factory of Pankajakasthuri Herbals India Pvt. Ltd, Thiruvananthapuram, Kerala, India.
 
Dosage– 10g/day [5g twice daily]
                                                                                              |
| EVALUATION CRITERIA                                | Clinical, Haematological and Biochemical assessments                                                                                                                                                                                                                                                                                                                                                                                                                                                                                         |
| ASSESSMENT SCHEDULE                                | 
The initial assessment will be done before the commencement of the study (0th day) and simultaneously the study will be initiated. Further assessment will be done on the 3rd month and will be followed on every six months till the completion of the study (i.e. 90th, 180th, 365th, 545th& 730th day). Interim data analysis will be done at the end of first six months (180th day) and report will be published in reputed journal.
 |
| STATISTICAL CONSIDERATION                          | Appropriate statistical analysis will be performed. p value ≤0.05 indicates that the study is statistically significant.                                                                                                                                                                                                                                                                                                                                                                                                              |
| DURATION OF STUDY                                  | The initial study period is 24 months, if required the study can be extended.                                                                                                                                                                                                                                                                                                                                                                                                                                                                |
| REFERENCE THERAPY                                  | Placebo and Standard of Care (SOC) will be given to control groups. In the study groups the trial drug and SOC will be                                                                                                                                                                                                                                                                                                                                                                                                                       |

|                                 |                                                                                                                                                                                                                                                                                                                                                                                                                                                                                                                                                                                                                                                                                                                   |
|---------------------------------|-------------------------------------------------------------------------------------------------------------------------------------------------------------------------------------------------------------------------------------------------------------------------------------------------------------------------------------------------------------------------------------------------------------------------------------------------------------------------------------------------------------------------------------------------------------------------------------------------------------------------------------------------------------------------------------------------------------------|
|                                 | 
given. Placebo for this trial will be given in the similar form as that of the trial drug. Placebo must be consumed according to the same procedures and guidelines as DiabetEaze Powder.
                                                                                                                                                                                                                                                                                                                                                                                                                                                                                                                  |
| CRITERIA FOR EVALUATION: | 
Efficacy:
 
 
• Fasting Blood Sugar
 
• Post Prandial Blood Sugar
 
• Oral Glucose Tolerance Test
 
• HbA1c
 
• Urine Sugar
 
• Investigation for Vitamins & Minerals
 
• Investigations for Diabetic Nephropathy
 
• Investigations for Diabetic Cardiopathy
 
• Investigations for Diabetic Neuropathy
 
• Investigations for Diabetic Retinopathy
 
• Other Laboratory investigations– CBC, Lipid Profile, LFT, RFT, CRP, Urine Examination etc.
 
 
Safety:
 
 
• ADR/AEs using MedDRA
 
• RFT & LFT
 
 |

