## **DURATION OF THE STUDY**

The initial study period is 24 months. If required, the study can be extended.

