### **STUDY COMPLETION AND END OF THE STUDY**

This trial will be considered complete (i.e. the scientific evaluation will be complete) following the evaluation of final outcome data. Investigators will continue the study if required. The End of the trial refers to the date of last visit (Day 730) or last schedule assessment for the last subject. The end of trial occurs after the study completion and after the last subject has discontinued the trial.

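### A Day 180 analysis is to be published while follow-up runs to Day 730, under one p ≤ 0.05 rule with no confirmatory time point named and an extension option without a criterion

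*Protocol*

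**What the plan says.** The Assessment Schedule row of the Clinical Trial Summary sets visits at Days 0, 90, 180, 365, 545 and 730. It then states "Interim data analysis will be done at the end of first six months", identified as Day 180, "and report will be published in reputed journal". The trial-design description under Conduction of Trial and Assessments, and the section on assessing the effect of the trial drug, repeat both the analysis and its publication. This is therefore a planned feature and not a stray phrase.

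The Statistical Consideration row gives the only significance rule: a p value "≤0.05 indicates that the study is statistically significant". The rule is attached to the study as a whole, not to a visit, endpoint or analysis. The Plan of Statistical Analysis adds only that suitable tools will be used.

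On length, the Summary says "The initial study period is 24 months, if required the study can be extended", and Duration of the Study repeats it. Study Completion and End of the Study says that the trial is complete once final outcome data have been evaluated, and continues: "Investigators will continue the study if required". None of these places says what would make an extension necessary.

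The Summary and the Methodology section both label the design open.

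**The concern.** Three features act together.

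- **Two occasions for a claim.** There are two analyses, one threshold and no statement of which analysis decides the trial. A p value of 0.05 or less at Day 180 could be reported as the trial's result. So could one at Day 730 if Day 180 is negative. The chance that at least one is falsely positive is above 5%.
- **Results released during follow-up.** If the six-month paper reports results by group, subjects, site staff and the sponsor learn which group appears to be ahead while outcome data are still being collected. Drop-out, use of other treatments and symptom reporting may then respond to it. Symptom reporting matters here because quality of life in terms of direct symptoms is a primary objective (Study Objectives).
- **Extension without a criterion.** With no trigger fixed in advance, a decision to prolong the study could be taken after group results are known, and could depend on them.

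**Working it through.** **Inputs from the protocol**

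- Threshold: p ≤ 0.05 (Statistical Consideration). Sidedness is not stated; two-sided is assumed, so the critical value is 1.960.
- Analyses: Day 180 and the final one at Day 730.
- Overall type I error: none is stated, so there is no figure of the plan's own to reproduce. One two-sided test at 0.05 gives 5% by definition.

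**Input that must be assumed**

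The correlation ρ between the Day 180 and Day 730 test statistics is not given. If the same subjects contribute to both, it is roughly the within-subject correlation of the outcome between the two visits. A range of 0.3 to 0.9 is shown.

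**Two-look false-positive rate, one endpoint and one contrast**

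Under the null hypothesis, with (Z₁, Z₂) bivariate normal with correlation ρ,

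P(at least one positive) = 0.05 + 0.05 − P(|Z₁| > 1.960 and |Z₂| > 1.960).

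| ρ | P(both positive) | P(at least one positive) |
|---|---|---|
| 0 (limit) | 0.0025 | 1 − 0.95² = 0.0975 |
| 0.3 | 0.0049 | 0.0951 |
| 0.5 | 0.0093 | 0.0907 |
| 0.7 | 0.0165 | 0.0835 |
| 0.9 | 0.0296 | 0.0704 |

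The rate is therefore about 7% to 9.5% over the assumed range. It applies only if a positive result at either time may be claimed.

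**If only Day 730 counts**

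The error rate is P(|Z₂| > 1.960) = 0.05 for every ρ. A descriptive look at Day 180 takes nothing from it.

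**Follow-up exposed to published results**

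730 − 180 = 550 days, and 550/730 = 75%. This is a per-subject maximum. Writing and publication take time after the analysis, and subjects recruited early will be past Day 180 when the last subject reaches it. The protocol text gives neither a recruitment period nor a publication date, so the actual share cannot be calculated.

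**Extension**

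No arithmetic applies. The Summary and Duration of the Study allow an extension at any time and without a criterion. Study Completion and End of the Study mentions continuation directly after the evaluation of final outcome data. Neither wording prevents the decision from following a view of group results, whether at Day 180 or at the end.

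**The case against.** **A statistical analysis plan, which is not shown, may hold an alpha rule.** This stands as far as it goes: the absence of alpha spending from the protocol is not a finding in itself. But such a plan would have to qualify the undifferentiated 0.05 rule that the protocol prints. Nor could it undo a publication made during follow-up or supply the missing limit on extension. Those are matters of conduct that the protocol itself fixes.

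**The protocol does not say that the Day 180 analysis compares groups, or that 0.05 is to be applied at both times.** Correct. The text speaks only of an interim analysis and a report, and the 0.05 rule names no visit. Comparison by group is an inference, though a natural one for a report of a randomized controlled trial, and nothing excludes it.

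**There is no early-stopping rule, so there need be no inflation.** Partly right. The inflation is conditional on a claim being allowed at either time. The protocol leaves that open because it names no confirmatory time point.

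**The trial is open, so staff already know the allocation.** Knowing a subject's group is not knowing which group is ahead; publication adds the second. The protocol also mentions a placebo and unblinding, which leaves the degree of blinding unclear, but the point about publication holds either way.

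**Sponsor and ethics oversight exist.** Publication of Results requires sponsor approval, and substantial protocol changes need ethics committee approval, which might cover an extension. These provisions say who approves. They do not say when group results may be released or on what grounds the study may be prolonged.

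**Stronger readings that the text does not support.** A reader might count a test at each of the five post-baseline visits; the protocol schedules assessments there and plans only one interim analysis. A reader might also conclude that an extension makes the final p value meaningless. A later extension does not by itself spoil a Day 730 test; the defect is that the grounds for extending are left open.

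**Conclusion.** The point holds, with limits. The protocol commits to analysing at Day 180 and publishing while follow-up is planned to Day 730, does not hold the report back until follow-up ends or restrict it to pooled data, and leaves undecided which analysis its 0.05 rule governs. The inflation to about 7% to 9.5% rests on three assumptions: two-sided tests, a correlation between 0.9 and 0.3, and freedom to claim success at either time. It is not a demonstrated error rate of the trial. The effect of published results on later conduct is a risk that cannot be quantified from the document; it arises if the report is by group and appears before follow-up ends. The extension clause adds a separate weakness, namely that no criterion shields the decision from knowledge of group results.

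**What to change.** Change the Assessment Schedule, Statistical Consideration and Duration of Study rows, and the sections that repeat them, to say that:

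1. Day 730 is the sole confirmatory time point, and the 0.05 rule applies to that analysis only.
2. The Day 180 analysis is descriptive and supports no claim of significance. Until the Day 730 data are locked, only pooled or baseline data are published.
3. Any extension leaves the Day 730 primary analysis where it is and is not decided on by-group results.

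If the six-month paper is essential, the alternative is to make Day 180 the sole confirmatory analysis and label all later data descriptive.

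Dividing alpha between the two times is not proposed. It would need a defined primary contrast, and the protocol has three primary objectives and six groups without naming one.

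The cost is protocol wording, plus a six-month paper that is restricted or delayed. Under the alternative, the paper is kept and the Day 730 data lose confirmatory standing.

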## JUSTIFICATION FOR CONDUCTING THE TRIAL

The Dietary Supplement Health and Education Act (DSHEA) of 1994 define a dietary supplement as a “product taken by mouth that contains a dietary ingredient intended to supplement the diet.” These dietary ingredients may consist of “vitamins, minerals, herbs, amino acids, and other botanicals and substances such as enzymes, organ tissues, glandulars, and metabolites” [9]. According to the 2017 Standards of Medical Care in Diabetes, “Each person with diabetes should be actively engaged in education, self-management, and treatment planning with his or her health care team, including the collaborative development of an individualized eating plan” [10]. Thus nutritional therapy is much essential for Pre-diabetic and Diabetic patients for providing optimum diabetes care.

Studies have shown that poor eating habits are the main factor behind the disease DM. Also, diabetic subjects usually follow unhealthy eating habits which impair daily health and wellbeing. This habit can also affect the mental health, energy levels, complexion, and overall well-being. More over it is scientifically proven that DM subjects have decreased levels of Vitamin A, C and E. To overcome this, a supplement can be used to fill in nutritional gaps of the diet. Conventional medical system had a great deal to offer in this regard. Various ingredients in DiabetEaze Powder such as Amalaki, Krishna Jeeraka, Shigru, Kalamegha, Ragi and Yava provides minerals, micro elements and amino acids which are essential for a diabetic person to overcome the oxidative stress. Also Vitamin B complex, C and E in Amalaki, Krishna Jeeraka, Shigru, Kalamegha, Ragi, Yava, Vrikkaphala and Panasa will help to overcome oxidative stress, boost the immune system and reduces the risk of development of various diabetic complications. DiabetEaze powder also ensures that person is getting a measurable amount of essential nutrients which make up for the poor nutrient content of the many foods one eats.

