## STUDY OBJECTIVES

### Primary objective:

- ❖ Clinical Nutritional Assessment of DiabetEaze Powder in Type 2 DM
- ❖ To assess the variation in Quality of Life in terms of direct symptoms.
- ❖ To assess the role of DiabetEaze Powder in managing nutritional inadequacy in DM.

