### **Participant recruitment process**

Subjects must meet the inclusion criteria and have none of the exclusion criteria in order to be eligible for randomization in this study. Subjects who meet all eligibility criteria, and have signed informed consent will be included under Baseline study visit. Once the subject is randomized the Sponsor Representative or the Study Investigator will provide the study staff with a unique randomization number for the subject. At the Randomisation, subjects will be centrally, dynamically randomised in a 1:1:1:1:1:1 fashion to each of the following six groups, namely two controls and four trial groups each with 30 subjects.

1. Group 1: Control group for Pre-Diabetes (30 subjects).
2. Group 2: Study group for Pre-Diabetes (30 subjects).
3. Group 3: Control group for Type II DM (30 subjects).
4. Group 4: Study group for Type II DM – Study drug will be administered as add on therapy with Allopathic medicines (30 subjects).
5. Group 5: Study group for Type II DM – Study drug will be administered as add on therapy with AYUSH medicines (30 subjects).
6. Group 6: Study group for Type II DM – Study drug will be administered along with life style management (30 subjects).

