## **PLAN OF STATISTICAL ANALYSIS**

Appropriate statistical tools will be used for the study.

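### The protocol's only decision rule, p ≤ 0.05 for the study as a whole, is tied to no outcome, comparison or visit, so as written it does not hold a 5% error rate

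*Protocol*

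**What the plan says.** The Statistical Consideration row of the Clinical Trial Summary says that a p value "≤0.05 indicates that the study is statistically significant". Significance is attached to the study, not to a test. The Plan of Statistical Analysis adds only: "Appropriate statistical tools will be used for the study".

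The rule could be applied to the following:

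- **Primary objectives.** There are three, unranked: "Clinical Nutritional Assessment of DiabetEaze Powder in Type 2 DM"; "To assess the variation in Quality of Life in terms of direct symptoms"; and "To assess the role of DiabetEaze Powder in managing nutritional inadequacy in DM". None comes with a variable, an instrument or a time point.
- **Groups.** Participant recruitment process sets up "six groups, namely two controls and four trial groups each with 30 subjects". Groups 4, 5 and 6 (Type 2 DM) face one control, Group 3. Group 2 (pre-diabetes) faces Group 1.
- **Efficacy measures.** Criteria for Evaluation lists eleven unranked bullets. Five are glycaemic: fasting sugar, post-prandial sugar, OGTT, HbA1c and urine sugar. Only one is nutritional by name, "Investigation for Vitamins & Minerals", and it does not say which vitamins or minerals.
- **Times.** There are five post-baseline visits (Days 90, 180, 365, 545 and 730). An interim analysis at Day 180 is to be published.

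Hypoglycaemic effect and the effect in pre-diabetes are secondary objectives.

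**The concern.** A threshold of 0.05 limits the false-positive risk to 5% only when one test is named in advance. Here the threshold is written as a verdict on the whole trial, and the protocol does not limit which result can trigger it. Two things follow.

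First, the chance of declaring a positive study when the product does nothing rises with the number of results that are allowed to count.

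Second, the result that counts need not answer the trial's main question. The primary objectives concern nutrition and quality of life in Type 2 DM, yet five of the eleven efficacy bullets are glycaemic. One low p value for a glucose measure would satisfy the sentence as written, and it could do so in the Day-180 publication.

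**Working it through.** **Inputs from the protocol.** Threshold 0.05; three primary objectives; three Type 2 DM study groups sharing one control; one pre-diabetes pair; eleven efficacy bullets; equal groups of 30 (6 × 30 = 180, which agrees with the stated sample size).

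**Assumptions not in the protocol.** Two-sided tests (sidedness is not stated); one test per objective or bullet; no true effect anywhere; equal correlation ρ between outcomes, varied from 0 to 0.8. Several bullets are panels, so one test per bullet is a low count.

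**Step 1: the plan's own figure.** For k independent tests, the chance of at least one p ≤ 0.05 is 1 − 0.95^k. With k = 1 this is 0.05. The rule therefore holds 5% for a single test and for no larger number.

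**Step 2: independent tests.**
- k = 3 (one outcome, three Type 2 DM groups): 1 − 0.95³ = 14.3%
- k = 9 (three outcomes × three groups): 1 − 0.95⁹ = 37.0%
- k = 33 (eleven bullets × three groups): 1 − 0.95³³ = 81.6%

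**Step 3: allow for the shared control and correlated outcomes.** Each comparison is z = (study group − control)/√2 in standardised units. Two comparisons that share Group 3 then have correlation 0.5, which lowers the figures in step 2. Simulated chance of at least one |z| ≥ 1.96 (200,000 runs for one or three outcomes, 60,000 for eleven):

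| Tests that may count | ρ = 0 | 0.3 | 0.5 | 0.8 |
|---|---|---|---|---|
| 1 outcome × 3 Type 2 DM groups | 12.5% | – | – | – |
| 3 outcomes × 3 Type 2 DM groups | 33.2% | 31.6% | 29.4% | 23.5% |
| 11 bullets × 3 Type 2 DM groups | 76.9% | 70.6% | 60.8% | 39.8% |
| 3 outcomes × all 4 comparisons | 42.5% | 41.1% | 38.2% | 31.1% |
| 3 outcomes × all 4 comparisons, plus Day 180 | 60.7% | 59.1% | 55.4% | 46.2% |

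The last row also assumes that Day 180 carries half the final information, so the correlation between interim and final statistics is √0.5.

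**Step 4: the proposed rules, same method.**
- One outcome, one comparison, one visit: 5.0%
- One outcome, three Type 2 DM comparisons, Bonferroni at 0.05/3 = 0.0167: 4.6%

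**The case against.** The best defence is that the sentence is only a clumsy way of stating the 0.05 threshold. It follows a promise of suitable analysis and does not say that any p value will do. The choice of test and the multiplicity method are commonly left to a statistical analysis plan, which may exist. The absence of such a method from the protocol is indeed no fault. What remains is that the protocol states a study-level rule of its own, and that rule is wrong as worded. A later plan that named one test would still conflict with it.

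A reader might infer more than the documents support:

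- **That a false-positive trial is likely.** On the three primary objectives in Type 2 DM the risk is 23% to 33%, below one half. It exceeds one half only on wider counts, and even the eleven bullets give 40% at correlation 0.8. The 77% end needs five measures of glycaemia to be mutually independent, which is implausible. The first and third primary objectives also overlap, so the upper end of their range is generous.
- **That the efficacy list is mostly glycaemic.** It is five of eleven.
- **That every bullet will be tested in every group at every visit.** That grid would be 11 × 4 × 5 = 220 tests, with 220 × 0.05 = 11 positive by chance. The protocol nowhere commits to it, and itemised post-baseline assessment lists appear only for Days 90, 180 and 730.
- **That a glycaemic result is declared to answer a primary objective.** The objectives keep the two apart. The gap lies in the decision rule, which does not.

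**Conclusion.** The point holds: the stated rule is wrong as written. With the shared control modelled, it gives 12.5% for a single outcome across the three Type 2 DM groups. It gives 33% to 23% for three primary outcomes across those groups, roughly five to seven times the nominal rate, and 77% to 40% if the eleven bullets may count. These sizes rest on one test per item and on correlations of 0 to 0.8, neither of which the protocol gives. The defect itself needs no assumption beyond there being more than one eligible test. The rule also allows a secondary glycaemic result to make the study significant. It should be corrected before any results are analysed, including those for the Day-180 report.

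**What to change.** Delete the sentence and state instead:

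1. Two-sided 0.05 applies to one pre-named primary outcome, at one named visit, for one named Type 2 DM comparison with Group 3. The sponsor chooses the comparison. The outcome must be one that the trial measures and must match a primary objective, for example one named item from the vitamins and minerals panel. The Justification says that "it is scientifically proven that DM subjects have decreased levels of Vitamin A, C and E", but the protocol does not show that any of these is measured, so the assay has to be confirmed first.
2. Alternatively, keep all three Type 2 DM comparisons for that outcome with a multiplicity adjustment, such as Bonferroni at 0.0167 or Dunnett.
3. Any further confirmatory claims follow in a fixed order, each tested only if those before it succeeded. A quality-of-life step needs a named instrument, because none appears in the efficacy list or the visit assessments.
4. Pre-diabetes (Group 2 vs Group 1) is a secondary test, either placed in that order or declared outside the 5% claim. Run beside the primary test at its own 0.05, it would give 1 − 0.95² = 9.8% across the two populations.
5. The Day-180 report is labelled interim and makes no success claim.
6. Everything else is reported as estimates with confidence intervals.

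**Cost.** The change is to wording, but naming the confirmatory comparison is substantive and would go through the protocol's own amendment and ethics approval route. Fewer results can be called significant. Keeping three comparisons also costs power. As an illustration with 30 per group, no dropout and an assumed standardised difference of 0.73, the expected z is 0.73 × √(30/2) = 2.83. Power is about 81% at 0.05 (Φ(2.83 − 1.96)) and about 67% at 0.0167 (Φ(2.83 − 2.39)).
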